**2.3.2. Secondary End-Points**

The secondary outcome measures a composite outcome defined as survival to 60 days or survival to transplantation at any time post therapy. Comparison will be made to historical hospital controls who had IPF exacerbations.

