**RESEARCH PROTOCOL ABSTRACT:**

This is an open-label Phase I/II trial to assess the feasibility and safety of combined plasma exchange (PEX), rituximab, and conventional corticosteroid administration on the outcome of hospitalized patients with acute IPF exacerbations. The specific aims of this study are:

1. To assess the feasibility and safety of combined PEX, rituximab, and conventional corticosteroid administrations for the treatment of hospitalized patients with acute IPF exacerbations by monitoring indices of respiratory (PaO2) and cardiovascular function during the treatment interval.
2. To assess the efficacy of combined PEX, rituximab, and conventional corticosteroid administrations for the treatment of hospitalized patients with acute IPF exacerbations on patient survival in comparison to historical controls. Patient survival for this investigation will be defined using the composite outcome of 60 day survival and/or survival to lung transplantation.

Subjects between 18 and 80 years of age who have a confirmed diagnosis of IPF, and meet all the study requirements will be enrolled in this study. A total of 10 subjects of both genders and all ethnic backgrounds with acute IPF exacerbations hospitalized at UPMC will be enrolled in this study.

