Idiopathic pulmonary fibrosis (IPF) is an interstitial lung disease characterized by inflammation and fibrosis of lung parenchyma affecting gas exchange. IPF has a poor prognosis with median survival of approximately 3 years from the time of diagnosis. Although IPF is chronic in nature and usually slowly progressive, some patients may experience an accelerated phase of the disease that has a very poor prognosis, with death occurring in a few days to weeks. Acute IPF exacerbation has been defined as an acute, clinically significant deterioration, without unidentified cause, of respiratory status in patients with underlying IPF. Current criteria for acute IPF exacerbations include a combination of the following that have occurred within a 30 day period: exacerbation of dyspnea and/or evidence of abnormal gas exchange, as defined by a lower partial pressure of arterial oxygen (PaO2)/percentage of inspired oxygen (FiO2) ratio or a decrease in PaO2; new bilateral radiographic opacities; and an absence of infection or another identifiable etiology such as left heart failure, or pulmonary embolism.

The etiology of IPF remains elusive,1-3 and the mechanism(s) leading to acute exacerbations of this disease are especially mysterious.4 The majority of IPF patients with acute exacerbation are admitted to intensive care units with acute respiratory failure. To date, there is no proven successful treatment for acute IPF exacerbation that has been shown to prolong survival, aside from lung transplantation. Treatment of acute IPF exacerbations traditionally has consisted of high-dose corticosteroids (pulse solumedrol), but unfortunately, many patients do not respond to treatments. During the past year, 42 patients were admitted to UPMC PUH with IPF exacerbations and the hospital mortality rate was approximately 50%. The majority of these patients died awaiting lung transplantation. Accordingly, the development and demonstration of a feasible medical treatment that prolongs short-term patient survival, could act as a bridge to transplantation. This would have a hugely beneficial effect by enabling more of these otherwise doomed patients to have the only currently recognized treatment for this disease process.

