**SECTION 3 – HUMAN SUBJECTS**

**3.1 SUBJECT POPULATION**

Subjects for this investigation will be recruited without regard to gender, race, or ethnic background. The anticipated age range for the study population will be >18 years old based upon the target disease population. The study population will be recruited from the inpatient populations at UPMC.

Ten adult subjects of both genders and all ethnic backgrounds with acute IPF exacerbations hospitalized will be eligible for enrollment. All subjects must provide written informed consent prior to participation. Surrogate consent will be obtained for subjects on mechanical ventilation, until the subjects are able to confirm the consent process when they are able to communicate. Based on the referral populations of UPMC, we expect ~40% of eligible subjects will be women and ~10% will be non-Caucasian.

We should be able to achieve these recruitment goals, as the number of potentially eligible patients is far greater than these projected numbers (42 IPF exacerbations at UPMC in the past fiscal year). We anticipate too that nearly all eligible subjects (or their surrogates) will likely elect to participate in this trial, given the poor response to current treatment.4 We expect to enroll the proposed study population within one calendar year.

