**3.2 INCLUSION CRITERIA**

The inclusion criteria have been selected to isolate a patient population with advanced idiopathic pulmonary fibrosis with a disease exacerbation. The exclusion criteria are selected to not enroll patients with an alternative cause for a respiratory decompensation (ie infection, pulmonary embolism) and to exclude patients with increased risk for the associated intervention (corticosteroids, plasmapheresis and ritiximab). Patients with a coagulopathy are excluded to minimize the risk of catheter insertion associated with the intervention.

1) A diagnosis of idiopathic pulmonary fibrosis that fulfills American Thoracic Society Consensus Criteria.1*

2) Unexplained worsening or development of dyspnea or hypoxemia within 30 days leading to the current hospitalization.

3) Radiographic imaging showing ground-glass abnormality and/or consolidation superimposed on a background of reticular or honeycomb pattern consistent with UIP.

4) Intent on the part of the treating physician to use high dose steroid therapy as a therapeutic effort to treat a diagnosis of acute IPF exacerbation.

In addition to strict adherence to current consensus criteria,1 IPF patients have serologic determinations of antinuclear antibody (ANA), rheumatoid factor (RF), anti-glomerular basement membrane antibody (AGBM), and anti-nuclear cytoplasmic antibodies (p-ANCA and c-ANCA) as standard of care diagnostic tests. Results of these serologic tests will be retrospectively used to substantiate the absence of confounding autoimmune syndromes in trial subjects, with implications for final data analyses and reporting.

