**3.3 EXCLUSION CRITERIA**

1. Diagnosis of documented infection based upon clinical evaluation and microbial testing.
2. Diagnosis of thromboembolic disease by clinical assessment.
3. Diagnosis of an additional etiology for ALI/ARDS based upon clinical assessment to include sepsis, aspiration, trauma, inhalational injury, acute pancreatitis, drug toxicity, blood product transfusion reaction, or stem cell transplantation.
4. Diagnosis of congestive heart failure that accounts for the hypoxemia.
5. Presence of active hepatitis B infection.
6. Coagulopathy defined as an INR > 1.8, PTT > 2 x control, and platelet count < 50K.
7. Hyperosmolar state or diabetic ketoacidosis to suggest uncontrolled diabetes mellitus or uncontrolled hypertension (systolic BP > 160 mm Hg and diastolic BP > 100 mm Hg) which would contraindicated the use of corticosteroids.
8. Hemodynamic instability defined as a vasopressor requirement which would contraindicate the use of plasmapheresis.
9. History of reaction to blood products, murine-derived products, or prior exposures to human-murine chimeric antibodies,
10. History of malignancy.
11. Inability or unwillingness to accept a blood transfusion.
12. Inability or unwillingness to complete post- treatment surveillance for 60 days.
13. Diagnosis of major comorbidities expected to interfere with subjects study participation for 60 days.

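### Historical controls need not meet the trial's eligibility criteria or start from a comparable day, so selection alone could produce a survival difference in Aim 2

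*Protocol*

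**What the plan says.** - **Comparator.** Protocol 2.3.2: "Comparison will be made to historical hospital controls who had IPF exacerbations". Section 2.4.1 plans 100 of them with assumed survival of 50%, against 10 treated subjects with hoped-for survival of 90%, and states a power of 0.6.
- **Outcome.** Section 2.3.2 uses "a composite outcome defined as survival to 60 days or survival to transplantation at any time post therapy".
- **Treated subjects.** Section 3.2 lists four inclusion criteria and 3.3 lists thirteen exclusions. Exclusion 8 is "Hemodynamic instability defined as a vasopressor requirement which would contraindicate the use of plasmapheresis", 10 is any history of malignancy, 12 is inability or unwillingness to complete 60 days of surveillance, and 13 is "Diagnosis of major comorbidities expected to interfere with subjects study participation for 60 days". Consent and enrolment take place on Day 0 (2.2.2).
- **Source of the 50%.** The only observed control figure is in 1.3: "42 patients were admitted to UPMC PUH with IPF exacerbations and the hospital mortality rate was approximately 50"%. Section 3.1 describes the same 42 as only potentially eligible.
- **Adjustment.** Section 2.4.2 describes covariates for gas exchange and ventilation-free days, chosen for imbalance under random assignment. The trial is non-randomized (2.1), and no adjustment is described for survival.
- **Serology.** Section 3.2: "Results of these serologic tests will be retrospectively used to substantiate the absence of confounding autoimmune syndromes in trial subjects", with consequences for the final analyses.
- **Age.** The abstract has "Subjects between 18 and 80 years of age", 3.1 has "The anticipated age range for the study population will be >18 years old", and 3.2 and 3.3 give no limit.

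**The concern.** A comparison with historical controls is only as good as the match between the groups at time zero. Here the treated group is filtered and, as written, the control group is not.

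The filters bear on the outcome. Patients on vasopressors or with a malignancy are removed from the treated group, and exclusions 12 and 13 look ahead over the same 60 days as the endpoint. Treated subjects also cannot die between admission and Day 0. A control counted from admission can.

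Who the controls are is a design matter that 2.3.2 itself settles, so it is not a detail left to an analysis plan. Section 2.4.1 builds a hypothesis test on it and expects that high efficacy could show through. If the groups differ in prognosis at the start, that test cannot separate the regimen from the selection.

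**Working it through.** **1. The plan's own figure.** Inputs from 2.4.1: n₁=10, n₂=100, p₁=0.90, p₂=0.50, power 0.6. Alpha, sidedness and test are not stated; I assume two-sided 0.05.

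- Pooled rate = (10×0.90 + 100×0.50)/110 = 59/110 = 0.536
- SE under the null = √[0.536×0.464×(1/10+1/100)] = 0.1654
- SE under the alternative = √[0.09/10 + 0.25/100] = 0.1072
- Continuity correction = ½(1/10+1/100) = 0.055
- Power = Φ[(0.40 − 0.055 − 1.96×0.1654)/0.1072] = Φ(0.194) = 0.577

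This rounds to the stated 0.6, so I do not dispute that figure. Exact enumeration gives 0.63 for the Yates-corrected chi-square and 0.75 for two-sided Fisher. All of these take the 50% as given.

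**2. What selection alone could do.** Suppose a share f of control-type patients would fail the trial's criteria and a proportion s of those survive. With overall survival at 0.50, eligible patients survive at (0.50 − f·s)/(1 − f). An inert regimen would show this rate in the treated group. The values of f and s are my assumptions; the document gives neither. The last column is the exact probability, over all 10-by-100 outcomes, that two-sided Fisher p≤0.05 favours the regimen.

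| f | s | Eligible survival | Spurious gain (points) | Favourable significant result |
|---|---|---|---|---|
| none | – | 50% | 0 | 1.9% |
| 0.10 | 0.30 | 0.47/0.90 = 52.2% | 2.2 | 2.5% |
| 0.20 | 0.30 | 0.44/0.80 = 55.0% | 5.0 | 3.6% |
| 0.20 | 0.10 | 0.48/0.80 = 60.0% | 10.0 | 6.7% |
| 0.30 | 0.20 | 0.44/0.70 = 62.9% | 12.9 | 9.1% |
| 0.40 | 0.20 | 0.42/0.60 = 70.0% | 20.0 | 18.5% |
| 0.40 | 0.10 | 0.46/0.60 = 76.7% | 26.7 | 32.4% |

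At round values of 55%, 63% and 75% the probabilities are 3.6%, 9.3% and 28.4%. With the Yates-corrected test they are lower: 2.2% at 55%, 7.5% at 65% and 20.5% at 75%, against 1.1% with no selection. If selection ran the other way and treated subjects had an underlying 45% or 40%, the Fisher figure would be 0.9% or 0.4%, and the bias would hide a benefit.

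**3. Same screen on both groups.** With a common null rate of 55%, 60%, 70% or 75%, the favourable Fisher rate is 1.9%, 1.8%, 1.1% or 0.4%, so the inflation goes. Fisher power for 90% with 100 controls is then 0.62, 0.45 or 0.13 at control survival of 55%, 60% or 70%, against 0.75 at 50%.

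**The case against.** **The protocol is silent about the controls; it does not say that they are unscreened.** A reader might infer that any hospital patient qualifies. Section 2.3.2 does not say so. What stands is that nothing requires a screen.

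**Thirteen exclusions overstate the contrast.** The definition of an exacerbation in 1.3 already rules out infection, left heart failure and pulmonary embolism. Controls who meet it pass exclusions 1, 2 and 4 and much of 3. Exclusions 5, 9 and 11 have little evident bearing on 60-day survival. Exclusion 6 joins its laboratory limits with an and, so as written it removes few patients. I accept this: the case rests mainly on 8, 10, 12 and 13 and on the missing index date.

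**The direction is not fixed.** Section 3.2 aims at advanced disease and requires intent to give high-dose steroids, and 4.2 expects many ventilated subjects under surrogate consent. Trial subjects could be as sick as general admissions, or sicker. This stands, so the direction is probable, not certain.

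**Serology.** A reader might infer that antibody-positive subjects will be dropped and that this favours the regimen. Section 3.2 never says that anyone is removed, and any removal would follow serology, not outcome. Against 50/100, 8/10 gives p=0.099; removing a death gives 8/9 and p=0.035, but removing a survivor gives 7/9 and p of about 0.17. What stands is that the step is described for trial subjects only and its effect on the analysis is left open.

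**Hospital mortality.** The 50% in 1.3 is a planning figure. Section 2.3.2 attaches the comparison to the composite outcome, so this is a weakness of the power statement, not a bias in the comparison.

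**Standing of the endpoint.** Survival is secondary, the trial is called exploratory, and the primary outcomes of feasibility and safety are untouched. This lowers the severity but does not remove the point.

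**Conclusion.** The point holds in this form: controls are not required to meet the trial's criteria or to start from a comparable day, and no survival adjustment is planned, so a difference can arise from selection alone, probably in the regimen's favour.

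The document does not support the stronger conclusion that the comparison must favour an inert regimen. It does not establish that the controls are unscreened, and some features of the trial population could pull the other way.

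The size is not known. Over the assumed range (10–40% of controls ineligible, 10–30% of those surviving), the spurious gain in step 2 runs from about 2 to 27 points and the favourable Fisher rate from 2.5% to 32.4%, against 1.9% without selection. These figures assume control survival of 50%, two-sided testing at 0.05 and Fisher's test, which 2.4.2 names for adverse events and not for survival.

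This should be fixed. It is not critical, because the comparison is secondary and exploratory.

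**What to change.** **In 2.3.2:**
- Define controls as consecutive prior admissions in a stated period who meet, on chart review, those 3.2 and 3.3 criteria that records can show, including high-dose steroid treatment and one age limit. The abstract and 3.1 must first be reconciled on age.
- Set control Day 0 at the start of high-dose steroid, which is also when the trial regimen starts, and score the identical composite outcome from that day.
- Keep all 10 enrolled subjects in the main analysis. Use any serology-based exclusion only as a sensitivity analysis applied in the same way to both groups.

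**In 2.4.1:** re-derive the 50% control survival and the power of 0.6 in the screened set. Describe the comparison as preliminary, because willingness and expected interference (exclusions 11 to 13) cannot be fully matched from charts.

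**Cost:** chart review, a protocol paragraph, and possibly fewer than 100 controls. The loss of controls matters less than the survival rate of those who remain. At 50% control survival, Fisher power for 90% is 0.75 with 100 controls, 0.72 with 70 and 0.64 with 42. With 100 controls at 55%, 60% or 70% survival it falls to 0.62, 0.45 or 0.13. That drop is no argument against screening: it shows how far the stated power depends on the assumed 50%.

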**2.4 STATISTICAL APPROACH**

**2.4.1 Sample Size and Power**

This is an exploratory observational trial to demonstrate feasibility and the statistical power analysis for the sample size is not appropriate. The sample size of 10 for this clinical trial is based upon: 1) exposing a minimum number of patients to potential risks of the experimental treatment while still obtaining useful information; 2) the intent to collect detailed and comprehensive data in each subject to provide comprehensive information relevant for design of a future larger trial, and also provide adequate specimens for the Ancillary Studies. This is an exploratory Phase I/II clinical trial focused on establishing proof-of-concept, and providing access to a novel treatment regimen in patients with a very high risk of hospital mortality.

Given the nature of this initial, exploratory and uncontrolled clinical trial, definitive power calculations are speculative. Nonetheless, high efficacy of the experimental treatment (as we anticipate) could produce evidence of same, given the usual high mortality of historical control patients. We are planning a study with 10 experimental subjects and 100 historical control subjects. A conservative estimate of survival among historical controls is 50%. If our treatment results in 90% survival, we will be able to reject the null hypothesis that the failure rates for experimental and control subjects are equal with probability (power) 0.6.

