**2.4.2 Statistical Analysis**

The data analysis for the primary aim begins by describing the sociodemographic, and medical characteristics of the population at baseline. Descriptive statistics, including measures of central tendency and dispersion, will be computed for continuous data (e.g., age). Frequency distributions will be estimated for categorical data (e.g., gender). Mixed effects regression models will be used to assess the treatment effects on gas exchange. Main effects will include treatment, intubation status, time, as well as a treatment by time interaction and random effects for slope and intercept. Additional main effects may include those baseline characteristics not balanced by random assignment, if any are identified. A linear regression model will be used to assess the effect of treatment on the number of ventilation-free days. As with the mixed effects model, main effects will include treatment, intubation status and characteristics not balanced by random assignment, if any are identified. For both the mixed effects model and the linear regression model, the model assumptions (e.g., normality of residuals) will be investigated. If the assumptions are violated, transformations will be investigated. If adequate transformations cannot be identified, nonparametric approaches will be utilized.

Treatment-emergent adverse events are defined as any new event reported after enrollment, or any event that is worse in severity than at any time during the baseline period. Intergroup differences in percentages of treatment-emergent adverse events will be assessed using Fisher's exact test or chi-square test.

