**4.2 INFORMED CONSENT PROCEDURES**

The consent process will begin via one of two possible pathways:

1) Referral of the prospective participant to the investigators/research coordinator by a physician who has knowledge of the proposed research, and obtains patient/surrogate consent for the research team to approach the patient/surrogate.

2) Individuals who have provided signed IRB-approved HIPPA compliant consent for participation in clinical trial research registries.

Prior to performing any of the study procedures the subjects must provide informed consent. The information about this study will be given to subjects in language understandable to subjects. Only physician investigators will present the study to the potential subjects. The physician investigator will verbally present a general outline of the research plan, including inclusion and exclusion criteria, to the prospective participant. The consent form, outlining the design of the study, will include the risks and benefits of participating, and will be reviewed and the investigator will answer any questions. Prospective participants may take as much time as required to make an informed decision. Written informed consent will be obtained from each participant prior to performing any research study procedures.

In addition, older potential study participants whose competency to consent is in question will be tested for sufficient comprehension and recall of the information presented. Prospective subjects who do not remember the important facts about participation in the research study after repeated testing will not be included in the study. The investigators will also assess whether a participant understands experimental procedures over time, including assessment throughout the full duration of participation in the study.

Proxy consent:Given the nature of the study population, which frequently requires mechanical ventilation with sedation, surrogate consent, will occur in a proportion of the study population. This will remain a valid consent until the patient is fully alert, and aware, and can provide a second consent to continue participation in the study.

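### The only hypothesis stated for survival against historical controls is unadjusted, so a difference in baseline intubation could create or mask an apparent benefit

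*Protocol*

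**What the plan says.** Protocol section 2.3.2 defines the secondary endpoint: "The secondary outcome measures a composite outcome defined as survival to 60 days or survival to transplantation at any time post therapy". It then states that "Comparison will be made to historical hospital controls who had IPF exacerbations". It names no restriction, matching or adjustment of those controls.

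Section 2.4.1 gives the sizes, "We are planning a study with 10 experimental subjects and 100 historical control subjects", and assumes 50% survival in controls and 90% on treatment. With these it claims power 0.6 to "reject the null hypothesis that the failure rates for experimental and control subjects are equal". That is the only hypothesis the protocol states for this comparison.

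Section 2.4.2 specifies two treatment-effect models. For gas exchange, "Main effects will include treatment, intubation status, time" and a treatment-by-time interaction. For ventilation-free days, a linear model that again contains treatment and intubation status. Both may add baseline characteristics left unbalanced by random assignment. Section 2.1 describes the trial as non-randomised. Section 2.4.2 names no model or covariate for survival.

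Sections 3.2 and 3.3 do not restrict enrolment by intubation status. Section 4.2 describes the study population as one "which frequently requires mechanical ventilation with sedation" and provides for surrogate consent.

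**The concern.** Aim 2 is the protocol's efficacy question, and it is answered against patients who were not treated concurrently or allocated at random. Intubation status is a baseline factor that the protocol already uses in its other two treatment-effect models, and both intubated and non-intubated patients can enrol. If survival differs by intubation status and the two groups differ in their intubated share, a comparison of unadjusted failure rates mixes that difference with the effect of the regimen. The allowance for unbalanced characteristics does not help: it belongs to the other two models and refers to a random assignment that this trial does not have.

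Section 2.4.1 says the results should inform the design of a larger trial and that high efficacy could show itself even at this size. A survival difference produced by case mix, or a real one hidden by it, would mislead that decision.

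**Working it through.** **1. The plan's own figure.** Inputs from section 2.4.1: 10 subjects at 90% survival, 100 controls at 50%, power 0.6. Significance level and sidedness are not stated; two-sided 0.05 is assumed. For two crude proportions with a continuity correction:

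- pooled rate = (9 + 50)/110 = 0.536
- standard error under the null = √[0.536 × 0.464 × (1/10 + 1/100)] = 0.165
- standard error under the alternative = √[0.9 × 0.1/10 + 0.5 × 0.5/100] = 0.107
- correction = 0.5 × (1/10 + 1/100) = 0.055
- power = Φ[(0.40 − 0.055 − 1.96 × 0.165)/0.107] = 0.577 (unrounded inputs)

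Exact enumeration with the Yates chi-square gives 0.628. Both round to the stated 0.6. Without a continuity correction the normal approximation gives 0.760; Fisher's exact test gives 0.746. The stated power is thus consistent with a two-proportion comparison without covariates, and it is not shown to be wrong.

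**2. Effect of intubation mix when the regimen does nothing.** Let f be the intubated share in the trial, and let s_I and s_N be survival in intubated and non-intubated patients. Expected trial survival is f × s_I + (1 − f) × s_N. The shares and stratum rates below are assumptions; each set is chosen so that control survival is 50%.

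- Mild: controls 40% intubated, s_I = 20%, s_N = 70%. Check: 0.4 × 0.2 + 0.6 × 0.7 = 0.50.
- Strong: controls 50% intubated, s_I = 20%, s_N = 80%. Check: 0.5 × 0.2 + 0.5 × 0.8 = 0.50.

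The last column is the exact probability of a two-sided Fisher p ≤ 0.05 in favour of treatment, summed over Binomial(10, expected survival) × Binomial(100, 0.5).

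| Scenario | Trial share intubated | Expected trial survival | Apparent difference | Chance of significance for treatment |
| --- | --- | --- | --- | --- |
| Equal mix | as controls | 50% | 0 | 1.9% |
| Mild | 20% | 0.2 × 0.2 + 0.8 × 0.7 = 60% | +10 points | 6.7% |
| Mild | 0% | 70% | +20 points | 18.5% |
| Strong | 20% | 0.2 × 0.2 + 0.8 × 0.8 = 68% | +18 points | 15.4% |
| Strong | 10% | 0.1 × 0.2 + 0.9 × 0.8 = 74% | +24 points | 26.2% |
| Strong | 0% | 80% | +30 points | 41.4% |

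An uncorrected chi-square gives slightly higher values (2.5% with equal mix, 45.9% in the last row). A continuity-corrected test is more conservative (0.628 against Fisher's 0.746 in step 1) and would give lower ones.

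**3. The other direction.** In the strong scenario, a trial with 80% intubated expects 0.8 × 0.2 + 0.2 × 0.8 = 32% survival against 50%. That is an apparent deficit of 18 points with no effect of the regimen, and it would offset a true benefit of that size.

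**4. After standardising.** In the strong scenario with 10% of subjects intubated, reweighting the control strata to the trial's mix gives 0.1 × 0.2 + 0.9 × 0.8 = 74%. The comparison becomes 74% against 74%, and the spurious 24 points disappear.

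**The case against.** Several points against this are sound.

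- **Section 2.4.1 is a planning statement.** It calls power calculations speculative, names no test and does not say that the comparison will be unadjusted. A separate analysis plan could add covariates. This stands: a reader might infer that the protocol has committed itself to a crude survival test, and the text does not go that far. It does state only an unadjusted hypothesis.
- **Intubation may be in the other models for their own reasons.** PaO2 is measured through an endotracheal tube or a face mask (section 2.3.1), and ventilation-free days depend directly on intubation. This also stands. Those models do not prove that the sponsor regards intubation as a survival confounder; they show that it is a baseline factor the protocol already plans to use.
- **A lower intubated share in the trial is not shown.** A reader might infer that the consent requirement and the vasopressor exclusion favour the trial group. But surrogates may consent for ventilated patients, section 3.1 expects nearly all eligible patients or their surrogates to take part, and the vasopressor exclusion can be applied to controls. The documents do not support a direction.
- **The magnitudes are assumed.** The 41% figure needs no intubated subject among ten, which sits badly with a population that often needs ventilation.
- **The endpoint is secondary and the trial exploratory.** Stratifying on one factor leaves other differences between subjects and controls.

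None of this removes the central point. If the comparison is made as stated, intubation mix and treatment effect cannot be told apart.

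**Conclusion.** The point holds in limited form. As stated, the survival comparison sets unadjusted failure rates in 10 subjects against those in 100 historical controls, in a non-randomised trial, and leaves out a baseline factor used in both other treatment-effect models. Imbalance in that factor could create or mask an apparent survival benefit, and the documents do not show which is more likely.

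With no treatment effect, the chance of a significant result favouring treatment moves from 1.9% with equal mix to about 7% to 19% in the mild scenario and 15% to 41% in the strong one. These ranges cover trial intubated shares from 20% down to none. They rest on assumed shares and stratum survival, the protocol's 50% control survival, and a two-sided Fisher test at 0.05. They show what could happen and do not predict it. Because the endpoint is secondary and exploratory, this is a worthwhile low-cost improvement and not a flaw in the primary aim.

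**What to change.** In sections 2.3.2 and 2.4:

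1. Apply the trial's eligibility criteria to the historical controls. This alone does not balance intubation, which is not an eligibility item.
2. Record intubation status at Day 0 for subjects and at a defined index date for controls.
3. Make the survival comparison either stratified by intubation status (an exact stratified test of Mantel-Haenszel type) or against a control rate standardised to the trial's intubation mix.
4. Report the crude comparison alongside, and describe the result as exploratory.

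The cost is one further chart item and one index date per control; the protocol does not define that date, so it must be constructed. If most of the ten subjects fall in one stratum, fewer controls contribute effectively and intervals widen, in a comparison whose stated power is only 0.6. One binary factor is about as much as ten subjects can carry, so other differences from the controls will remain and should be acknowledged in the report.
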